## 5. LAY DESCRIPTION

Sepsis is a life-threatening illness which arises when the body's response to an infection injures its own tissues and organs. Septic shock is a severe subset of sepsis characterised by low blood pressure such that the blood flow to tissues is inadequate. Septic shock is a medical emergency requiring urgent treatment to restore adequate blood flow to the tissues, as well as measures to control the underlying infection.

The conventional standard initial treatment for septic shock is to attempt to restore the blood pressure by giving IV fluids through a drip. International expert consensus guidelines recommend that 20-30 ml/kg (approximately 2-3 litres in an average adult) be administered during the first 3 hours of treatment. If this is not sufficient to correct the problem, an IV drip containing medication to raise the blood pressure is started. Many patients receive a combination of fluids and medications.

Despite the observation that there has been a reduction in deaths from sepsis in the past two decades, there is emerging evidence that IV fluids, particularly in excess quantities, are associated with harm in sepsis. An alternative is to give less fluid initially and start a medication drip earlier as a means of reducing the overall amount of fluid administered. There is currently uncertainty about which is best for patients, and as a consequence practice varies between these approaches. In addition, as mortality has fallen, there is an increasing focus on quality of life among survivors. People who survive septic shock can have severe lifelong problems including persistent organ failure, amputated limbs, psychological injury and impaired ability to function at the level they previously enjoyed.

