### 7.2 Hypothesis

We hypothesise that a restricted intravenous fluid volume and earlier introduction of vasopressors approach, compared to a larger initial intravenous fluid volume and later introduction of vasopressors approach to restore systemic arterial blood pressure, will increase the number of days alive and out of hospital at day 90 in patients presenting to the ED with early septic shock.

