### **10.9 Follow up at day 90, 6 and 12 months**

The descriptor for the person who is legally allowed to give consent will vary between jurisdictions. For the purposes of this protocol, the descriptor 'legally authorised representative' (LAR) describes the person who is legally allowed to give consent for the participant.

The participant or a LAR, if the participant has not regained capacity, will be contacted via a telephone call at 90 days, 6 and 12 months after randomisation for study follow up.

The day 90 follow up will be to establish survival at this time point and additionally to collect important information on readmissions and discharge to other hospitals, rehabilitation hospitals or long term nursing care facilities. This will inform the primary outcome for the study. As this information will be collected from the participant or (LAR), a diary/information collection sheet will be provided prior to hospital discharge to assist with this information collection.

At 6 and 12 months after randomisation, the participant or LAR will be contacted again via a phone call. This call will collect information quality of life and functional outcome information by the E-Q-5D and WHODAS 2.0 surveys.

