### 14.3 Serious adverse events

The baseline mortality of participant with septic shock is high. Such patients will frequently develop life-threatening organ failure(s) unrelated to the study interventions and despite optimal management. Therefore, events that are part of the natural history of the disease process or are expected complications of septic shock will not be reported as serious adverse events in this study. In particular, events already defined as study outcomes (e.g. death, readmission) will not be reported separately as serious adverse events unless they are considered to be causally related to the study intervention or are otherwise a concern in the investigator's judgement.

SAEs will be defined in accordance with the Note for Guidance on Clinical Safety Data Management: Definitions and Standards for Expedited Reporting (CPMP/ICH/377/95) (July 2000) as any untoward medical occurrence that:

- Results in death
- Is life-threatening
- Requires inpatient hospitalisation or prolongation of existing hospitalisation
- Results in persistent or significant disability/incapacity
- Is a congenital anomaly/birth defect
- Is an important medical event which may require intervention to prevent one of the previously listed outcomes

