### 14.4 Reporting

AEs and SAEs, which are deemed causally related to the study intervention by the investigator, will be collected from randomisation up to hospital discharge.

SAEs will be reported to the coordination centre within 24 hours of the site investigator becoming aware via completion of the SAE form on the website. Minimum data will include the patient study ID, nature of the event, commencement and cessation of the event, the investigators opinion of the relationship of the event to the trial

(possibly, probably or definitely related), and any treatment which was required. The investigator should notify the Institutional/Ethics Committee of the occurrence of the serious adverse event or any significant safety issues in accordance with local jurisdictional requirements/policy directives.

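### A causally related hospital readmission or post-discharge death is a reportable SAE under section 14.3 but falls outside the collection window in section 14.4

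*Protocol*

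**What the plan says.** Section 14.3 keeps natural-history events and expected complications of septic shock out of SAE reporting. It adds that "events already defined as study outcomes (e.g. death, readmission) will not be reported separately as serious adverse events" and continues directly with the exception: "unless they are considered to be causally related to the study intervention or are otherwise a concern in the investigator's judgement". One of the SAE criteria listed in the same section is "Requires inpatient hospitalisation or prolongation of existing hospitalisation", which any readmission to a ward meets.

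Section 14.4 then fixes what is collected and for how long: "AEs and SAEs, which are deemed causally related to the study intervention by the investigator" "will be collected from randomisation up to hospital discharge". It gives no number of days. Its next paragraph asks sites to report an SAE within 24 hours of learning of it.

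Other sections bear on the point:

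- Section 10.9 sets a telephone contact at day 90 to establish survival and to "collect important information on readmissions and discharge to other hospitals, rehabilitation hospitals or long term nursing care facilities".
- Section 12.1 follows participants to day 90, or to death if earlier, for the primary outcome.
- Section 12.2 lists vital status at fixed times, and admission and discharge dates including readmissions, as outcome data.
- Section 14.1 has SAE reports forwarded to the data safety monitoring committee (DSMC) or its delegated safety monitor.
- Section 10.2 caps the intervention at 24 hours after randomisation.

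**The concern.** The two adjacent sections give a site incompatible instructions for the same event. A readmission to hospital comes after a discharge from hospital. If the investigator thinks it was caused by the study intervention, 14.3 makes it an SAE, while 14.4 has already closed collection. The same is true of a related death after discharge. The route by which the DSMC sees individual safety events is the SAE report, so a related event after discharge has no stated path to the committee as an SAE.

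A second feature of the same sentence deserves attention. The window ends at an event that occurs after randomisation and that treatment may influence. Hospital length of stay is a tertiary outcome, and time out of hospital is a component of the primary outcome. Section 7.2 hypothesises that the vasopressors strategy "will increase the number of days alive and out of hospital at day 90". If treatment changes the hospital stay, the two arms would be observed for related AEs and SAEs for different lengths of time.

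**Working it through.** **The text, side by side.** The protocol states no figure for this point (no window in days, no expected number of SAEs), so the main check is a reading of the rules by type of event.

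| Event judged causally related | Reportable under 14.3? | Inside the 14.4 window? |
|---|---|---|
| Death during the index stay | Yes | Yes |
| ICU readmission during the index stay | Yes, if read as a readmission | Yes |
| Hospital readmission after discharge | Yes | No |
| Death after discharge | Yes | No |

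The second row is there because the outcome list in 12.2 mentions readmissions after ED, ICU and hospital admissions together, so the word can cover a return to ICU before discharge. The last two rows are the conflict.

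**Does other data collection close the gap?** The day-90 contact and the 12.2 list capture that a readmission happened, its dates, and vital status. They do not list the reason for a readmission, and cause of death is listed only for hospital mortality. No causality judgement and no SAE report is attached to any of these items. The fact of the event is kept, but the causality judgement and the SAE form are not.

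**Can the effect on window length be sized?** The available inputs are in section 13.1: mean DAOH-D90 of 60 days, SD 31, planned gain 7 days. These are the figures the plan uses. With two-sided alpha 0.05 and 90% power they give 413 per arm, 826 in total; 826 × 1.15 = 949.9 (stated 950); 950 / 0.95 = 1000 (stated 1000).

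Deaths by day 90 score zero (section 8.1). Write m for mortality by day 90 and H for survivors' mean days in hospital. Then mean DAOH = (1 − m) × (90 − H), so H = 90 − 60/(1 − m). The protocol does not give m for the planning data. As assumptions only, I take in-hospital figures from section 6: 8% (82 patients with septic shock in the observational study), 18% (sepsis in ICU) and 22% (its shock subgroup).

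| Assumed m | H at mean 60 | H at mean 67 if all the gain is through stay | m needed if all the gain is through survival, H unchanged |
|---|---|---|---|
| 8% | 90 − 60/0.92 = 24.8 | 90 − 67/0.92 = 17.2 | not possible |
| 18% | 90 − 60/0.82 = 16.8 | 90 − 67/0.82 = 8.3 | 8.4% |
| 22% | 90 − 60/0.78 = 13.1 | 90 − 67/0.78 = 4.1 | 12.9% |

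The last column is 1 − 67/(90 − H). At 18% and 22% the full 7 days can arise with no change in survivors' hospital days. Below about 10.4% (1 − 60/67) mortality alone cannot supply the gain, and some reduction in hospital days would be needed. The answer therefore turns on a mortality figure the protocol does not provide. H is also not the window length, because it includes readmission days, which lie after the window has closed.

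**The case against.** The strongest reply is that little is lost in practice. The intervention lasts at most 24 hours, so most events it causes should appear during the index stay. Readmissions and survival are recorded to day 90 at the same times in both arms. The 24-hour reporting rule runs from the site's awareness and carries no end date, and 14.4 does not say that the discharge meant is the index one, so a site that hears of a related event at the day-90 call is not expressly forbidden to report it. All of this stands, and it is why the point is minor. It does not remove the conflict: the collection sentence still ends at discharge, and nothing asks sites to judge causality on what they learn afterwards.

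Three stronger readings are tempting and are not supported.

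- A reader might infer that the 14.3 exception can never operate. It does operate, for in-hospital death and for ICU readmission within the index stay.
- A reader might infer that late ischaemic harm goes unrecorded, citing the list in section 5 ("persistent organ failure, amputated limbs, psychological injury"). That list describes problems of people who survive septic shock, not harms of treatment. Section 12.2 collects ischaemic events as complication outcomes with no stated cut-off at discharge, and section 14.2 deliberately keeps complication outcomes out of separate adverse event reporting.
- A reader might infer a biased comparison of SAE rates in favour of the vasopressors arm, and attach a percentage to it. Sections 8 and 13.2 plan no between-arm SAE comparison. The hypothesis concerns days alive and out of hospital, not a shorter stay as such. If deaths fall, patients who would have died early are observed to discharge instead, which could lengthen that arm's window.

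**Conclusion.** The inconsistency between 14.3 and 14.4 is real on the plain reading that discharge means the end of the index admission. It is confined to causally related hospital readmissions and causally related deaths after discharge. The window has no fixed length and may differ between arms if treatment changes hospital stay. That is a conditional weakness: its size and direction cannot be established from the protocol, and no percentage shortening should be quoted. Any such figure would combine an earlier trial's mean with in-hospital mortality from other cohorts, and it falls to zero if the gain comes through survival, which is possible at 18% or 22% mortality.

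Severity is minor, given the short intervention and the outcome data already collected to day 90 in both arms. No sample size or power figure is affected.

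**What to change.** Reconcile the two sections. Have 14.4 collect causally related SAEs, at least readmissions and deaths, to a fixed time from randomisation that is the same for every participant. The existing day-90 follow-up, or death if earlier, is an obvious choice because section 10.9 already asks about survival and readmissions then. Add a question on the reason for each readmission at that contact, and state that the 14.3 criteria apply to what is learned, so that a related event after discharge reaches the DSMC by the usual SAE route.

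The cost is protocol and case report form wording, an added question at an existing call, and a few more SAE forms. Events after discharge will be dated less precisely. Causality will be judged by investigators who know the allocation, partly from what the participant or legally authorised representative reports, and sometimes only after records are obtained from another hospital.

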## **15.FUNDING**

The ARISE FLUIDS trial is funded by the Medical Research Future Fund Rare Cancers, Rare Disease and Unmet Need grant scheme (APP1200084).

## **16.PUBLICATION POLICY**

All publications arising from the trial will comply with the requirements of the ANZIC-RC, the ANZICS CTG and ACEM CTN for group authorship. Publications will be authored on “behalf of the ARISE FLUIDS Investigators”. A writing committee will be convened from the membership of the management committee. Authors named in the journal by-line will meet the authorship criteria defined by the International Committee of Medical Journal Editors (ICJME). Membership of the ARISE FLUIDS Investigators group will comprise site investigators and other contributors and will be listed in the acknowledgement section of the paper. These will be designated contributors to the study in PubMed.

Funding bodies will be acknowledged in the publication.

## **17.TRIAL REGISTRATION**

This trial has been registered on clinical trials.gov NCT 04569942.

## 19.APPENDIX 1: OPT-OUT APPROACH AND THE NATIONAL STATEMENT

This trial meets the conditions for an opt- out approach as detailed in the National statement 2.3.6 as follows:

*a) involvement in the research carries no more than low risk to participants*

This trial where both trial arms are encompassed by the range of usual care in Australia and New Zealand, confers no greater clinical risk than receiving routine treatment. Refer to protocol section 11.3.

*b) the public interest in the proposed activity substantially outweighs the public interest in the protection of privacy*

This trial will address an important gap in the evidence base and has the potential to provide future guidance for bedside clinicians and optimise important patient-centred outcomes. As such it has significant public interest while privacy is protected by an opt-out approach and study design methods. Refer to protocol section 11.4.

*c) the research activity is likely to be compromised if the participation rate is not near complete, and the requirement for explicit consent would compromise the necessary level of participation*

Participants (when deemed competent) and/or their LAR will be approached as soon as reasonably possible after enrolment. An opt-out approach will maintain the right to voluntarily determine participation while easing participant/LAR burden in indicating that decision which explicit consent imposes. Refer to protocol section 11.6.1.

*d) reasonable attempts are made to provide all prospective participants with appropriate plain language information explaining the nature of the information to be collected, the purpose of collecting it, and the procedure to decline participation or withdraw from the research*

All participants and/or their LAR will be provided with written and verbal information to facilitate understanding of all aspects of the trial and the procedure for declining participation. Refer to protocol section 11.6.1.

*e) a reasonable time period is allowed between the provision of information to prospective participants and the use of their data so that an opportunity for them to decline to participate is provided before the research begins*

Participants and/or their LAR will be approached at the earliest reasonable opportunity to consider their ongoing participation in the trial. They will have the ability to decline participation at this point or at any future time through the mechanism described in the information sheet/ brochure. As this encompasses the use of data and follow up telephone calls at day 90 and at 6 and 12 months they can decline/withdraw from further participation at any time before these time points.

*f) a mechanism is provided for prospective participants to obtain further information and decline to participate*

The information sheet/brochure, as approved by the relevant ethics committee, will contain contact numbers/details on who can provide further information and how to decline participation. Refer to protocol section 11.6.1.

*g) the data collected will be managed and maintained in accordance with relevant security standards*

The trial will adhere to all relevant data collection security standards, including those of Monash University as the trial coordinating centre. Refer to protocol section 12.

*h) there is a governance process in place that delineates specific responsibility for the project and for the appropriate management of the data*

The specific responsibilities for the trial itself and the appropriate data management are detailed in protocol sections 3 and 12.

*i) the opt-out approach is not prohibited by state/territory, federal, or international law.*

The opt-out approach is one of the 2 possible approaches to consent this study may use. Where opt-out approach is not possible due to local state/territory laws, then consent will be sought as consent to continue as detailed in protocol section 11.6.2.
